The ten secondary outcomes are being assessed, reflecting hypothesised pathways of change leading to the primary outcomes. Four secondary outcomes focus on gender attitudes and responses to violence:Acceptance of VAWG amongst female garment workers: Acceptance of VAWG among female garment workers is being measured using statements adapted from the Gender Equitable Men (GEM) scale [25] and WHO multi-country study on women’s health and domestic violence against women [26].Gender equitable attitudes of management staff: Gender equitable attitude of the management staff is being measured using statements adapted from the GEM scale [25], WHO multi-country study on women’s health and domestic violence against women [26] and the South African study on men, masculinities, violence and HIV [27].Response to IPV amongst female garment workers: A single item explores women’s help seeking in response to IPV. The question heavily drew upon the WHO multi-country study questionnaire [26] and the SAFE questionnaire [28]. This question will only be asked to those who experienced physical and/or sexual violence during last 12 months.Knowledge of services in response to IPV amongst female garment workers: One question assesses the knowledge of the workers about where to seek help after experiencing IPV.

Two secondary measures assess women’s well-being:5.Self-esteem of female garment workers: The Rosenberg Self-Esteem scale is being used to measure self-esteem [29]. It measures global self-worth by measuring both positive and negative feelings about self. The scale is uni-dimensional and has shown strong convergent validity for men and women from different ethnic groups [30].6.Depression among female garment workers: Depression in the past week is being measured using the Center for Epidemiologic Studies Depression (CES-D) scale used widely in different settings (including Bangladesh) and showing high reliability and validity [31]. Each question is a statement and asked the respondent to answer how many days she has had particular feelings or ideas.

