Severe physical and/or sexual IPV during past 12 months	Questions asked for measuring physical and sexual violence during past 12 months	Never, once, few, many	10	–	–	Binary - never compared to once or more	Decrease
Witnessed or experienced workplace violence	In the past four weeks, how often have you experienced or witnessed a manager call a worker names?	Never, once, 2-3 times, many times	8	0.83		Mean	Decrease
Secondary outcomes							
Gender attitudes and responses to violence							
Acceptance of VAWG among female workers	In your opinion, does a man have good reason to hit his wife if she disobeys him?	4-point Likert: Strongly disagree, disagree, agree, strongly agree	6	0.69	–	Mean	Decrease
Positive gender attitudes among management staff	I think that a woman needs her husband’s permission to do paid work.	4-point Likert: Strongly disagree, disagree, agree, strongly agree	13	–	0.68	Mean	Decrease
Response to IPV	Did you go to any person/place for help when you experienced any physical or sexual violence during last 12 months?	Yes, no	1	–	–	Binary – yes compared to no	Increase
Knowledge of services in response to IPV	Do you know from where one can get help for such experience? If yes, where?	Yes, no	1	–	–	Binary – yes compared to no	Increase
Women’s well-being							
Self-esteem of the female garment workers	At times, You think you are no good at all.	4-point Likert: Strongly disagree, disagree, agree, strongly agree	10	0.76	–	Mean	Increase
Depression among female garment workers during past week	During the past week you thought your life had been a failure.	Rarely or none of the time; some or a little of the time; moderate amount of time; most or all of the time	13	0.87	–	Mean	Decrease
Management knowledge, practices and experiences							
Better management style of management staff	If you do not comply with your supervisor, you will not be rewarded	Very unlikely; Somewhat likely; Very likely	14	0.90	–	Mean	Increase
Correct knowledge regarding laws and policies	Are there laws/policies in this country that protect women from spousal violence?	Yes; no; don’t know	5	–	–	% correct compared to % incorrect	Increase
Positive attitudes regarding laws and policies	To your opinion - “Sexual remark and gesture is an act of workplace violence”	Strongly agree; agree; no opinion; disagree; strongly disagree	5	–		Mean	Increase

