### Sample size

For the worker survey, the sample size calculation was based on the primary outcome – physical IPV against female garment workers. Expecting 56% baseline prevalence of past year physical IPV experienced by the female garment workers (icddr,b unpublished data), and anticipating a 20% effect size, 5% level of significance and 80% power, the required sample size was 330 workers for both the intervention and control groups. To account for a 20% lost to follow up the sample size increased to 396 workers for both the groups, which was rounded up to 400. Thus, a sample of 100 workers would be required from each of the intervention and control factories, giving 800 in total.

For the management survey, the sample size calculation was based on gender inequitable attitudes among garment management staff. Anticipating 50% baseline prevalence of high or moderate gender equitable attitudes among the management staff, a 30% effect size, 5% level of significance and 80% power, the required sample size was 183 management staff for both intervention and control groups. Anticipating 10% loss to follow up, the sample size increased to 200 for both the groups. Thus a sample of 50 management staff would be required from each of the intervention and control factories, giving 400 in total.

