### Statistical methods: Data analysis

Intention-to-treat (ITT) analysis will be used for assessing the impact of HERrespect. Thus, all the workers selected for the study will be included in the analysis. The primary analysis will involve comparison between intervention and control factories for assessing the impact of full HERrespect intervention (group sessions and factory-wide mobilization) over control. First the data from intervention and control factories and baseline and endline samples will be compared and Chi-square (for categorical variables) and t-tests (for continuous variables) will be performed to test whether there are differences in prevalence of background characteristics. If differences between intervention and control factories and baseline and endline samples are evident, the pre-existing differences will be controlled in subsequent analyses. The impact of HERrespect intervention on main outcomes of interest will be assessed using risk ratios derived from binary regression analyses adjusting for baseline rates. All analyses will be adjusted for the potential factors associated with the outcomes of interest. The same approach will be followed for assessing the secondary outcomes.

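### The management survey's 80% power is for a two-proportion comparison, but Table 2 defines the management attitude outcome as the mean of 13 items, so the power statement does not describe the test of the listed outcome

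*Protocol article*

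**What the plan says.** In the protocol article, the Sample size section states that for the management survey "the sample size calculation was based on gender inequitable attitudes among garment management staff". The inputs are then given for the opposite pole of the construct and as a proportion: "Anticipating 50% baseline prevalence of high or moderate gender equitable attitudes among the management staff, a 30% effect size", with "5% level of significance and 80% power". The required number is 183, raised to 200 per arm (50 in each of eight factories, 400 in total) for 10% loss.

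Under Trial outcomes, the second secondary outcome is described as a scale: "Gender equitable attitude of the management staff is being measured using statements adapted from the GEM scale" and from two other sources. No categories are given. Table 2 lists it as positive gender attitudes among management staff: 13 items, four-point Likert, method of scaling *Mean*, expected change *Decrease*. The example item is "I think that a woman needs her husband’s permission to do paid work".

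The data analysis section specifies risk ratios from binary regression for the main outcomes and adds: "The same approach will be followed for assessing the secondary outcomes".

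**The concern.** The one outcome that justifies the size of the management survey has two forms. The sample-size paragraph treats each manager as above or below a threshold. Table 2 treats each manager as having a score. Table 2 marks other outcomes as binary or as percentage correct where that is meant, so *Mean* in this row reads as a deliberate choice.

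The analysis section does not settle the matter. Taken literally, risk ratios from binary regression would require the score to be cut, against Table 2. If Table 2 governs, the stated effect (a 30% relative change in a prevalence) and the 80% power do not describe the test that will be done.

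Two things are at stake. A reader cannot tell what difference on the listed outcome the survey was able to detect. And an analyst who follows the binary wording would discard information that the mean keeps.

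**Working it through.** **Inputs.** From the Sample size section: 50% baseline, 30% effect, 5% level, 80% power, 183 required, 10% loss, 50 managers in each of four factories per arm. Sidedness is not stated; two-sided reproduces the figure. From Table 2: a mean of 13 items. The article gives no SD and no target mean difference for this score, so standardised differences below are assumptions.

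**1. The plan's own figure.** Take p1 = 0.50, p2 = 0.50 × 1.30 = 0.65, average 0.575, difference 0.15.

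- Uncorrected: n = [1.960·√(2 × 0.575 × 0.425) + 0.842·√(0.50 × 0.50 + 0.65 × 0.35)]² / 0.15² = (1.370 + 0.582)² / 0.0225 = 169.3.
- With continuity correction: n′ = (n/4)·[1 + √(1 + 4/(n × 0.15))]² = 182.4, so **183 per arm**, an exact match.
- Reading the effect as 30 percentage points gives 45 per arm with the correction, so the effect is relative and 183 is per arm.
- Loss: 183/0.90 = 204, against 200 stated, which is close enough.

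The 183 is therefore a comparison of two proportions.

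**2. The same effect on the mean.** Assume that the binary version is a cut through a normal score with equal SD in both arms.

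- Shift = Φ⁻¹(0.65) − Φ⁻¹(0.50) = 0.385 SD.
- Power on the mean with 183 per arm = Φ(0.385·√(183/2) − 1.960) = Φ(1.726), about **96%**.
- Power when dichotomised, 50% v 65%: about **80%** with continuity correction and **83%** without.

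**3. What 183 per arm can detect on the mean.** Smallest difference at 80% power = (1.960 + 0.842)·√(2/183) = **0.29 SD**. For other assumed true differences, power on the mean is 48% at 0.20 SD, 67% at 0.25, 82% at 0.30 and 97% at 0.40.

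**4. Allowance for factories.** Steps 1 to 3 treat managers as independent, as the article's own calculation does. With 183/4 ≈ 46 managers per factory, the design effect is 1 + 45 × ICC. The article gives no ICC, so these are assumed.

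| Assumed ICC | Design effect | Effective n per arm | Mean, 0.29 SD | Mean, 0.385 SD | Dichotomised, 50% v 65% (no correction) |
|---|---|---|---|---|---|
| 0 | 1.00 | 183 | 80% | 96% | 83% |
| 0.01 | 1.45 | 126 | 64% | 86% | 68% |
| 0.02 | 1.90 | 96 | 53% | 76% | 56% |
| 0.05 | 3.25 | 56 | 34% | 53% | 36% |

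These are normal approximations. The few degrees of freedom from four factories per arm would lower them further.

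**5. Direction.** Objectives of the study aims to increase gender equitable attitudes among management. Table 2 labels the score positive attitudes and expects it to fall. The example item expresses an inequitable view, so a fall would be the desired change if agreement scores high and items are not reversed. In that case the label is wrong; otherwise the direction is. The article does not state how the items are scored.

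**The case against.** The strongest reply is that no harm follows. Both passages concern the same construct, and at the planned effect the mean has more power than the binary version, so sizing on the cruder form was conservative. That stands, and it rules out one tempting inference. A reader might conclude that the survey is underpowered, or that the choice of definition takes power from 80% down to roughly half. Figures of that size for a dichotomised outcome require a true effect smaller than the planned one, and the lowest also need a cut far from the 50% prevalence that the plan anticipates. The article supports neither.

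A second reply is that a threshold for the scale is detail that an article may leave to the full protocol or analysis plan. That also stands: the absence of the cut is not a fault here. Nor does the article support a suspicion that the cut will be chosen after the data are seen, since Table 2 publicly fixes a mean and any later cut would be a visible departure. What remains is a disagreement between two statements that the article does make.

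A third reply is that the binary-regression wording misfits every outcome scored as a mean, including the primary workplace violence scale. True; that is a wider point, and only its effect on this outcome is used here.

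Finally, baseline recruitment is complete (395 managers interviewed), so the sample-size basis is a historical record and should not be rewritten. That is accepted in the remedy.

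**Conclusion.** The concern holds as an inconsistency between the sizing and the outcome definition. The exact reproduction of 183 shows that the stated 80% power is for 50% v 65% on a dichotomised attitude measure; the listed outcome is a mean, and the stated analysis does not fit it. No detectable difference on the listed outcome is given.

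The mismatch alone does not reduce power. Under a normal score and independent managers, analysing the mean gives about 96% at the planned effect, against 80-83% for the binary version. Any shortfall would come from factory clustering, which affects both definitions, and its size rests on ICCs that the article does not supply.

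The weight is moderate. This is one of ten secondary outcomes, and neither the primary outcomes nor the worker sample is touched. It is still the only outcome used to justify the management survey, and the direction of its row in Table 2 also needs to be reconciled.

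**What to change.** 1. Keep the Table 2 mean of 13 items as the single definition. State that it will be analysed as a continuous score adjusted for its baseline value and will not be dichotomised, and amend the analysis section accordingly for this outcome.
2. State the scoring direction and make the label and expected change agree with the objective. If higher means more equitable, the expected change is an increase. Use one term, equitable or inequitable, in the sample-size paragraph.
3. Keep the 50% and 30% calculation as the recorded basis of the sample size, and say that it refers to a dichotomised version of the outcome.
4. Add a sentence such as: with 183 managers per arm, a difference of about 0.29 SD in the mean score is detectable at 80% power if managers are treated as independent; allowing for clustering in four factories per arm lowers this, for example to about 64%, 53% or 34% at assumed ICCs of 0.01, 0.02 or 0.05.

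The cost is a few sentences and one table cell. No further participants or data are needed, and the change can be made before the endline survey planned for September to November 2018. The drawback is that the effect is then reported in score units, which are less immediate than a percentage.

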### Eligibility criteria

Workers were eligible for the research if they were currently married and living with husband (necessary for measuring IPV) and had been working in the current factory for at least one year. All management staff in the factory management were eligible to participate in the study.

### Participant timeline

Recruitment of the factories was completed over a 6-month period from July to December, 2016. The study participants (workers and management staff) were recruited and the baseline data were collected during September to December, 2016. As soon as a factory was recruited baseline started in that factory while recruitment was continuing for other factories. Implementation of the intervention in the first intervention factory was started in November, 2016 once the survey was completed for that factory, and subsequently in other factories. The intervention was completed in August, 2017. The endline will be conducted from September to November 2018 (See Fig. 1).

**Fig. 1 Fig1:**
[figure not shown]
Participant timeline

### Recruitment and allocation

BSR works with a network of international brands and buyers via HERproject, a women empowerment initiative in the supply chain, in Bangladesh, and both intervention and control factories in HERrespect were recruited through buyers as per the selection criteria, through one-on-one engagement and a suppliers’ workshop. Four buyers participated in nominating eight factories (four intervention and four control) to join HERrespect. Participant factories had strict preference for being included as an intervention factory or control factory and were recruited on that basis. Care was taken to select control factories at a distance from the intervention factories to prevent potential contamination. Also, preference was given to factories that had not recently completed similar training programs or interventions in gender-based violence.

Each factory provided a self-selected list of 315 workers from their full list of workers. A listing was then carried out of these selected 315 workers within each factory mainly for the purpose of screening eligibility. Once eligibility had been established and agreement to participate given, 100 workers were randomly selected from each factory. The workers from the intervention factories were then assigned to group sessions and interviewed at baseline. If more than one worker belonged to the same household, one was chosen randomly for participating in the study. Each factory provided a self-selected list of 50 management staff having direct interaction with workers. This cohort of management staff are interviewed at baseline and endline. However, all management staff received the group sessions.

### Blinding

No one was blinded to their study arm allocation.

### Listing of workers

The listing of workers was carried out by eight trained female interviewers in each factory. A researcher from icddr,b and a designated person from the factory worked closely with the listing team. The factory provided space for conducting the listing interviews and allowed the workers to give 5 min for an interview to determine eligibility for the study.

### Baseline survey

#### Survey team, training and selection

The worker survey team consisted of 12 female interviewers, three female supervisors, three male field assistants, and one survey co-ordinator. The management survey team consisted of 6 male interviewers and one male supervisor. One quality control officer (QCO) was deployed for the surveys, and interviewed female management staff. One research officer was responsible for overseeing both the surveys. Shortlisted interviewer candidates for the worker survey received a 12-day training and the shortlisted interviewer candidates for the management survey received an 8-day participatory training on gender, violence against women, ethics, survey methods, the questionnaire, and use of tablets. The training included role play, pair practice, mock interview and discussion on survey techniques. A field test was included as part of the training and evaluation. The survey team members were finally selected based on their performance during the training and piloting.

#### Data collection tools

The questionnaire for worker and management surveys were developed in English and then translated into Bengali. The Bengali version of the worker questionnaire was pre-tested with 8 female garment workers and the management questionnaire was pre-tested with 10 garment management staff. Cognitive pre-testing was carried out for sections that had not been previously used in Bangladesh. The cognitive pre-test helped us in identifying sections and questions participants found difficult to understand and to adapt as appropriate. A pilot with 40 workers and 15 management staff was also conducted. The feedback received was incorporated into the questionnaire.

#### Data collection methods

Baseline data were collected between September to December 2016 using face-to-face interviews, with Personalized Digital Assistants (PDAs) to reduce data entry error as logic checks were built in. Workers’ interviews were conducted in private in a location convenient for participants outside the factory. According to the study participants’ choice 98% of workers were interviewed at their own home and 2% of them were interviewed outside of their home (e.g., relatives or neighbours home, Non-Government Organisation (NGO) office, etc.). The interviews took place in the evening after work during work days and in the day time during weekends and holidays. The usual time of the interviews was between 7 and 10 pm on work days and 9 am to 4 pm on weekends and holidays. The interviewers phoned the participants a day before the target interview date to schedule the interview and obtain directions for the interview venue. The interviews with the management staff were conducted in private within the factory during office hours. The appointments were arranged in advance.

Workers and management staff who were not available to be interviewed during baseline data collection were replaced. The replacement of a worker was done by randomly selecting another eligible worker from the same factory and the replacement of a management staff was done by the factory itself. But no replacement was made after the data collection had been completed.

#### Data quality monitoring and management

During fieldwork for the worker survey each interviewer was accompanied to the interview venue either by a supervisor or a field assistant. The supervisor and the field assistant made sure that the interview could be started in private. Once all the interviews started, the supervisor and the field assistant made rounds to check whether the interviews were uninterrupted. They also helped, if needed, to handle gatekeepers. The survey coordinator randomly visited the survey teams for spot checks.

The first level monitoring was performed by the supervisors by observing the quality of the interviews, keeping notes and discussing any problems at review sessions. A daily team meeting was mandatory for the survey team. Five percent of the study participants were revisited by the supervisors who administered a short questionnaire consisting of 11 questions focused mainly on identifying any problems in adhering to ethical guidelines and administering questions on particular topics. The second level of monitoring involved cross-checking of completed questionnaires. Each completed questionnaire was cross-checked by another interviewer who shared her observations in the team meeting. At the third level, the QCO rechecked each and every questionnaire on a daily basis, kept notes, provided feedback to the interviewers and supervisors, made corrections where possible, where necessary, guided the interviewer to make a phone call to the respondent to collect any missing data and to correct errors if possible, and sent the interviewer to revisit the respondent if it was necessary. They communicated with the researchers if the problems could not be resolved by themselves and communicated decisions back to the interviewers.

At the fourth level, the research officer and the researchers from icddr,b made frequent field visits, randomly checked filled-out questionnaires, observed interviews where possible and provided feedback to the survey team. Further, a computer-based data checking routine was developed by the icddr,b research team. The data were uploaded to the server every day after the data collection was completed for that day. Due to the efficiency of this system, inconsistencies in the data were identified within a short period of time. The research officer cleaned the data two days before the completion of the data collection in each study area. Problems identified in the data were communicated to the supervisors through the survey coordinator. The supervisor resolved the problems through discussion with the interviewer if possible. If necessary, the interviewer revisited the respondent and solved the issues consulting her. This actually enhanced prompt correction of the data by the QCO based on information received from the field. If the problems could not be resolved using this strategy the researchers were informed and the researchers suggested ways of resolving the issue depending on the nature of the problems.

The similar approach of monitoring was taken to ensure the quality of the management survey data, the only exception was that the survey coordinator was not involved with the monitoring of management data collection.

